**Methods:**

A randomized controlled trial will be conducted at Shalini Tai Meghe Super Speciality Centre with 70 CABG patients aged 45–65 years. Participants will be randomly allocated to Group A (conventional physiotherapy) and Group B (leg cycle ergometry with physiotherapy) for a 10-day intervention. Outcome measures include the Vancouver Scar Scale, Manual Muscle Testing, 6-Minute Walk Test, and Patient Health Questionnaire-9 (PHQ-9). Data will be analysed using the Mann-Whitney U test and the Wilcoxon signed-rank test; p<0.05 was deemed statistically significant.

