## Trial design

This study will follow a single-centre, parallel-group, randomized controlled trial design with an allocation ratio of 1:1. Participants will be randomly assigned to either the leg cycle ergometry plus conventional physiotherapy group or the conventional physiotherapy-only group.

The randomization sequence will be computer-generated using block randomization and implemented through sealed, opaque envelopes prepared by an independent researcher who is not involved in participant recruitment or assessment.

Because of the nature of the intervention, participants and treating physiotherapists cannot be blinded. However, all outcome assessors and data analysts will remain blinded to group allocation to reduce measurement bias.

The study will be conducted at a single tertiary-care teaching hospital with a dedicated cardiac rehabilitation unit. The trial follows the SPIRIT 2013 (Standard Protocol Items: Recommendations for Interventional Trials) guidelines for reporting clinical trial protocols and has been prospectively registered with the Clinical Trial Registry of India (CTRI/2025/03/084291) (Supplementary A). The planned CONSORT flow chart of participant recruitment and randomization is presented in Fig. 1.

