### Sample size calculation

The sample size was calculated in consultation with the institutional biostatistician using Cohen’s formula for comparing two independent means (Cohen, 1988), assuming an effect size (d) = 0.49, α = 0.05, and power (1–β) = 0.80.

Parameter estimates were derived from previous studies with comparable rehabilitation protocols in post-CABG patients [10, 13], the estimated sample size was 35 participants per group. Allowing for a 20% dropout rate, the final sample size was adjusted to 42 participants per group, resulting in a total of 84 participants.

The chosen effect size of 0.49 represents a moderate clinical difference expected in primary outcomes such as functional capacity, scar healing, and quality of life. This sample size is therefore adequate to detect a meaningful difference between groups in early post-CABG recovery.

$$\mathrm{n}=\mathrm{d2}(2(\mathrm{Z}\upalpha /2+\mathrm{Z}\upbeta)2 \cdot (2{\upsigma}2))=35$$

Mean group 1 (M1): 5.53

Standard deviation group 1: 1.75

Mean group 2 (M2): 4.60

Standard deviation group 2: 2.00

Correlation between groups: 0.5 10

Effect size: 0.49

Alpha level: 0.05 Power (1-beta): 0.8

Sample size- 35 in each group

Drop out 20%= 20x35/100=7 35+7=42

The revised sample size is 42 in each group

The total sample size required = 84 subjects (42 subjects in each group)

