### Statistical methods

All statistical analyses will be performed using IBM SPSS Statistics version or equivalent software. Descriptive statistics will be used to summarize demographic and baseline characteristics, with continuous variables expressed as mean ± standard deviation and categorical variables presented as frequencies and percentages. The Shapiro–Wilk test will be applied to assess data normality. For within-group comparisons (pre- and post-intervention), the paired t-test will be used for normally distributed data, while the Wilcoxon signed-rank test will be applied for non-parametric data. Between-group comparisons (experimental versus control) will be conducted using the independent t-test for normally distributed data and the Mann–Whitney U test for non-parametric data. Analysis of covariance (ANCOVA) will be employed to adjust for any baseline differences between groups. Missing data will be addressed using an intention-to-treat approach, applying the last observation carried forward method where appropriate. In addition, subgroup analyses may be performed based on age, sex, and baseline functional capacity to explore potential secondary interactions. A p-value of <0.05 will be considered statistically significant for all analyses.

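### No primary between-group analysis is fixed for either co-primary outcome, and ANCOVA is tied to baseline differences instead of being fitted always because baseline is prognostic

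*Protocol article*

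**What the plan says.** The trial is a "single-centre, parallel-group, randomized controlled trial design with an allocation ratio of 1:1" (protocol article, Trial design). Outcome measures names two co-primary outcomes, VSS and 6MWT, and has every outcome assessed at baseline and at the end of the 10-day programme.

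Statistical methods contains four elements that bear on this point:

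- A normality check on the trial data: "The Shapiro–Wilk test will be applied to assess data normality". Its result selects the independent t-test or the Mann–Whitney U test for the between-group comparison.
- Baseline adjustment: "Analysis of covariance (ANCOVA) will be employed to adjust for any baseline differences between groups". No covariate is named.
- Within-group testing: "For within-group comparisons (pre- and post-intervention), the paired t-test will be used for normally distributed data", with the Wilcoxon signed-rank test otherwise.
- One threshold, p < 0.05, for all analyses.

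Nothing in the section says which between-group result is primary for VSS or 6MWT, or whether the t-test or Mann–Whitney is applied to end values or to changes. The Abstract gives a shorter list: "Data will be analysed using the Mann-Whitney U test and the Wilcoxon signed-rank test". It mentions neither the t-test nor ANCOVA.

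**The concern.** There are two linked problems.

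**No single primary p-value.** For each co-primary outcome the text yields at least two eligible between-group results: the normality-selected test and ANCOVA. Both are judged at 0.05 and they are not ranked. The Abstract's list does not settle the matter. If the two disagree, the protocol does not say which one answers the question.

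**The wrong reason for adjusting.** With concealed 1:1 randomisation, baseline differences arise by chance. Baseline belongs in the model because it is expected to predict the end value, which removes residual variance whether or not the arms look different. Presenting ANCOVA as a remedy for imbalance invites its use only when imbalance is seen, and that gives up most of the precision a measured baseline could provide.

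The within-group tests are a lesser matter. The Objectives are comparative, and a pre–post change from the first postoperative days mixes natural recovery with any effect of ergometry. The text should therefore say that these tests are not evidence of a treatment effect.

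**Working it through.** **Inputs.** From Sample size calculation: "assuming an effect size (d) = 0.49, α = 0.05, and power (1–β) = 0.80"; 35 per group before dropout and 42 after; means 5.53 and 4.60; SDs 1.75 and 2.00; a correlation of 0.5 labelled as between groups. The formula uses Zα/2, so the test is two-sided. The correlation r between baseline and end value is not in the document. It is **assumed** at 0.3, 0.5 and 0.7.

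**The plan's own figure.** The stated method is "Cohen’s formula for comparing two independent means".

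- Two independent means, normal approximation: n = 2(1.960 + 0.842)²/0.49² = 65.4, so 66 per group (67 with the noncentral t). This does not give 35.
- Paired test: SD of the difference = √(1.75² + 2.00² − 2·0.5·1.75·2.00) = √3.5625 = 1.887. Then dz = 0.93/1.887 = 0.493, which gives 35 pairs.

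So 35 is a paired-test number. That is a separate matter, but it means that an unadjusted two-arm comparison starts well below 80% power.

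**Unadjusted power.** Noncentrality = d·√(n/2).

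- n = 42: 0.49·√21 = 2.245, power 60%.
- n = 35: 0.49·√17.5 = 2.050, power 52%.

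In simulation with normal data and 35 per arm, the normality-selected test applied to end values has power of 52% (r = 0.5) and 53% (r = 0.7), the same as the plain t-test to within simulation error.

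**ANCOVA always fitted.** Residual variance falls by the factor (1 − r²), so d is replaced by d/√(1 − r²): 0.514, 0.566 and 0.686.

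| Analysed per arm | Unadjusted | r = 0.3 | r = 0.5 | r = 0.7 |
|---|---|---|---|---|
| 42 | 60% | 64% | 73% | 87–88% |
| 35 | 52% | 56% | 64–65% | 80–81% |

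**ANCOVA only when baseline differs.** If the trigger is taken as p < 0.05 on baseline (an assumption, since the protocol sets no trigger), simulated power with 42 per arm is 60%–61% across the three correlations. With 35 per arm it is 52% at r = 0.5 and 54% at r = 0.7. Almost none of the gain is recovered.

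**Type I error per outcome (simulation, normal data, no true effect).**

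| Reporting rule | 42 per arm, r = 0.3 / 0.5 / 0.7 | 35 per arm, r = 0.5 / 0.7 |
|---|---|---|
| Normality-selected test alone | – | 5.2% / 5.2% |
| Fixed rule: ANCOVA if baseline p < 0.05, otherwise the selected test | 4.7% / 4.4% / 3.7% | 4.6% / 3.7% |
| Either the selected test or ANCOVA may be reported | 6.7% / 7.4% / 8.5% | 7.5% / 8.4% |

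A re-run (10,000 null data sets per setting) gave the same picture for the two-way choice. When the t-test, Mann–Whitney and ANCOVA were all freely available, the error reached 9.0%. A range of about 7%–10% per outcome is therefore a cautious statement; the two-way choice alone lies in its lower part.

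**The case against.** **ANCOVA may be meant always.** The sentence sets no threshold and contains no conditional, so it can be read as fitting ANCOVA every time in order to remove chance imbalance. That is a fair reading. On it the precision is kept and the 60%–61% figure for conditional use falls away. ANCOVA still stands beside the t-test or Mann–Whitney with neither called primary.

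**The rule may be harmless.** A reader might infer that choosing the test after seeing the data inflates Type I error in itself, or that the error exceeds 10%. The documents do not support either. Followed as a fixed rule there is no inflation, and the Shapiro–Wilk step alone is nearly harmless on normal data. Inflation needs selective reporting among the available results. Figures of 10.6%–11.0% (35 per arm) arise only if a change-score t-test is added, and the protocol does not name one.

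**The gain is uncertain.** This stands. No baseline-to-end correlation is given, and the 0.5 in Sample size calculation is labelled as between groups, so it cannot serve as one. Baseline falls on postoperative day 1–2, when the scar is new and walking may be limited, so a low correlation is plausible for either co-primary outcome.

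**Within-group tests.** A reader might infer that significance in one arm only will be presented as efficacy. Nothing says so; between-group comparisons are specified separately. A clarifying sentence is enough.

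**An unseen analysis plan may settle this.** It may, and model details can properly be left to it. But the published text states a data-driven choice and a rationale for ANCOVA, and its Abstract lists different tests. Those statements need correcting in any case.

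**Conclusion.** The point holds. The protocol names no primary between-group analysis for VSS or 6MWT, gives imbalance instead of prognostic value as the reason for ANCOVA, and lists different tests in the Abstract.

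With 42 analysed per arm, always adjusting would add about 4, 13 and 27–28 percentage points of power at assumed correlations of 0.3, 0.5 and 0.7. With 35 per arm the gains are about 4, 12 and 28. These figures assume d = 0.49, approximately normal data and a linear baseline relation. The comparator is the unadjusted test on end values, so the gain is forgone only if ANCOVA is not the analysis relied on.

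The Type I error of about 7%–10% per outcome is conditional on a free choice between results; it is not a property of the rule if followed as fixed. Adjustment does not repair the sample size: on the normal approximation, 80% power with 42 analysed per arm needs a correlation of about 0.6, and with 35 about 0.7.

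**What to change.** In Statistical methods:

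1. State one primary analysis for each co-primary outcome: ANCOVA of the end-of-programme value on arm, with the baseline value of the same measure as covariate, always fitted, reported as an adjusted mean difference with 95% confidence interval.
2. Make Mann–Whitney a sensitivity analysis, and drop the Shapiro–Wilk test as the means of selecting the primary test.
3. State that within-group pre–post tests are descriptive and are not evidence of a treatment effect.

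In the Abstract, bring the list of tests into line.

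The cost is wording. No patient, visit or measurement is added, because baseline is already collected. Trial status gives version 1.0, no amendments and recruitment expected to finish in August 2026, and the analysts are to be blinded, so the change can be made and dated before allocation is revealed. The gain depends on a usable baseline value, which matters most for 6MWT on postoperative day 1–2. The sample-size calculation needs its own correction.

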## Introduction

Coronary artery bypass grafting (CABG) is foundational to managing multivessel coronary artery disease. Although saphenous vein grafts (SVGs) may be considered for non-LAD targets, the right ITA (RITA) and radial artery (RA) are associated with improved outcomes [1]. Post-operative cardiopulmonary health is severely compromised with impaired pulmonary and respiratory function mediated by such factors as chest wall pain, decreased respiratory muscle strength, reduced exercise capacity and exercise tolerance, and anxiety with the resumption of more vigorous physical activity [2]. CABG remains one of the most commonly performed cardiac surgeries worldwide, yet post-operative complications continue to influence early recovery and hospital outcomes. Physiotherapy in the ICU was recently incorporated and is starting to work on the concept of early mobilization, as well as its importance in the practice of early mobilization [3]. Structured ICU exercise prescription helps prevent respiratory complications, preserve muscle strength, reduce mortality and disability risk, and promote psychological well-being. The objectives of cardiac rehabilitation (CR) are to promote independence, psychological stability, stress reduction, social reintegration, and restoration of physical capacity [4]. CR is a multidisciplinary, individualized program that addresses the functional and physiological limitations of patients recovering from heart disease [5, 6]. As a fundamental part of every cardiac rehabilitation program (CRP), regular physical activity can improve functional work capacity in cardiac patients after coronary artery bypass graft surgery [7]. Supervised exercise-based cardiac rehabilitation (CR) has been strongly recommended in recent years as an important adjunct therapy following CABG, with well-documented benefits associated with improved prognosis after revascularization [8]. Most usual-care CR in bypass patients is based on aerobic training, and an increasing body of literature has recommended the concomitant application of lower limb resistance training to enhance the beneficial effects of CR, including increased skeletal muscle strength (particularly lower limb muscle volume), an important peripheral factor influencing cardiac function [9]. Despite this, the majority of available research has focused on general aerobic training, with limited attention to targeted lower-limb rehabilitation following saphenous vein graft harvesting. CABG patients who undergo saphenous vein graft harvesting frequently experience lower limb complications such as edema, pain, and delayed scar healing, which can limit mobility and hinder participation in early cardiac rehabilitation. Phase I cardiac rehabilitation refers to the early, in-hospital phase of recovery typically spanning the first 2–10 days for after CABG surgery. It focuses on early mobilization, pulmonary care, and gradual restoration of physical function. While international guidelines such as those from the American Heart Association (AHA) and the European Society of Cardiology (ESC) emphasize early rehabilitation, implementation in developing countries like India remains inconsistent due to limited resources and lack of structured physiotherapy frameworks. Although several international trials have assessed aerobic training after CABG, few have specifically focused on targeted lower-limb rehabilitation addressing donor-site recovery, particularly within early Phase I hospital settings. This evidence gap highlights the need for structured, low-cost interventions such as leg cycle ergometry in resource-limited cardiac units. In the Indian healthcare setting, standardized in-hospital CR protocols are still evolving, highlighting the importance of evaluating feasible, evidence-based interventions during this early recovery. Despite the growing emphasis on early rehabilitation, there is a paucity of randomized controlled trials evaluating structured lower-limb exercises, such as leg cycle ergometry, during Phase I recovery in post-CABG patients.

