**Fig. 1 Fig1:**
[figure not shown]
Planned CONSORT flow chart

Final analysis will include all participants completing the study per protocol and intention-to-treat principles.

This diagram outlines the projected flow of participants through the study in accordance with CONSORT 2010 guidelines. Actual participant numbers and reasons for exclusion will be updated upon study completion.

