#### Outcome measures

All outcomes will be assessed at two time points: baseline (post-operative day 1–2, before intervention) and at the end of the 10-day Phase I rehabilitation period (post-operative day 10). Assessments will be conducted by blinded physiotherapists in the hospital setting.

This trial has two co-primary outcomes: (1) scar healing measured by the Vancouver Scar Scale and (2) functional capacity measured by the 6-Minute Walk Test. Secondary outcomes include muscle strength (MMT) and quality of life (PHQ-9).

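### With no assessment between baseline and the final visit, last observation carried forward can only impute zero change, which shrinks a real effect and, with unequal missingness, can create a false one

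*Protocol article*

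**What the plan says.** The Statistical methods section names a single device for missing data: "Missing data will be addressed using an intention-to-treat approach, applying the last observation carried forward method where appropriate". It gives no criterion for when the method is appropriate and no alternative for when it is not.

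The Outcome measures section sets the schedule: "All outcomes will be assessed at two time points". The first is on post-operative day 1–2, before the intervention. The second is "at the end of the 10-day Phase I rehabilitation period (post-operative day 10"). The Data collection method section runs the programme to post-operative day 11, but it adds no intermediate outcome assessment. The schedule covers both co-primary outcomes, the Vancouver Scar Scale and the 6-Minute Walk Test, and the two secondary outcomes.

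The Sample size calculation section makes a planning allowance for losses: "Allowing for a 20% dropout rate, the final sample size was adjusted to 42 participants per group".

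The caption to Fig. 1 describes the analysis set: "Final analysis will include all participants completing the study per protocol and intention-to-treat principles".

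**The concern.** Last observation carried forward presupposes at least one observation after the start of treatment. Here there is none, so the rule becomes baseline carried forward. A patient who misses the final visit is scored as unchanged since one or two days after surgery.

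Two things are at stake. If there is a true effect, the imputed zeros dilute it in proportion to the fraction missing. If the arms lose patients at different rates and patients generally change over the programme, the rule produces a between-group difference that has nothing to do with treatment. The imputed zeros also enter the planned within-group tests.

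The analysis set is a connected, smaller matter. Read literally, the Fig. 1 caption analyses completers, who have no missing final values to impute. The Statistical methods section imputes under intention-to-treat. As worded, the two places leave the primary set open.

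**Working it through.** **Inputs from the protocol article**
- 42 per arm, 20% dropout allowance, d = 0.49, α = 0.05, with Zα/2 in the formula implying a two-sided test (Sample size calculation).
- Two assessments (Outcome measures).
- Independent t-test between groups when data are normal (Statistical methods).

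The plan's 42 reproduces as 35 + 0.20 × 35 = 42. An allowance of 20% on 42 is 8.4, so about 8 patients per arm.

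**Assumptions not in the documents**
- Baseline and final SD are both 1, with correlation 0.5.
- Missingness is unrelated to outcome.
- Both arms share a common recovery g of 0, 1, 2 or 3 SD.

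Each patient contributes either a baseline or a final value, so the correlation does not enter a test on final values.

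**Expected difference under the rule.** Let δ be the true effect and qE, qC the missing fractions in the experimental and control arms. Baseline means are equal by randomisation, so

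difference = (1 − qE)(g + δ) − (1 − qC)g = (1 − qE)δ + (qC − qE)g.

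**Variance of the analysed final value.** In an arm with missing fraction q and mean change c, it is 1 + q(1 − q)c².

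**Case 1: 20% missing in each arm, δ = 0.49.** The difference is 0.8 × 0.49 = 0.392 SD, whatever g is. At g = 1 the control variance is 1 + 0.16 × 1² = 1.16 and the experimental variance is 1 + 0.16 × 1.49² = 1.355. Their mean is 1.258, so the SD is 1.12 and the standardised effect is 0.392/1.12 = 0.35. Power by simulation, t-test on final values:

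| Common recovery g (SD) | Carried forward | Observed cases |
|---|---|---|
| 0 | about 42% | about 51% |
| 1 | about 35% | about 51% |
| 2 | about 27% | about 51% |
| 3 | about 19% | about 51% |

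For reference, 42 complete patients per arm give about 60% power at d = 0.49. That this is below 80% is a separate matter concerning the sample size formula. The comparison here is between columns.

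**Case 2: no true effect, 25% missing in one arm and 15% in the other.** The false difference is (0.25 − 0.15) × g = 0.1g.

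| Common recovery g (SD) | False difference (SD) | Type I error |
|---|---|---|
| 0 | 0 | about 5% |
| 1 | 0.1 | about 7% |
| 2 | 0.2 | about 11% |
| 3 | 0.3 | about 14% |

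Swapping which arm loses more patients reverses the sign. Observed-case analysis stayed at about 5% under the same assumptions.

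**Case 3: no true effect, 20% missing in each arm.** The difference is 0 and type I error stays at about 5%. The between-group test remains valid.

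A repeat simulation of all three cases (40,000 runs each) agreed to within about one percentage point.

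**The case against.** The strongest reply is that the harm depends on figures the documents do not give. They state no expected recovery, and no passage predicts unequal losses; 25% versus 15% is an illustration. The 20% is a planning allowance, not a forecast. With no common recovery there is no false difference, and an analysis of change scores (SD 1) would then keep about 51% power, as for observed cases. All of this stands, and it is why the tables start at 0 SD. It does not restore the estimate: at 20% missing in each arm, a true effect is still multiplied by 0.8.

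The qualifier in Statistical methods also makes the rule less than unconditional. But it names no alternative, and no missing final value in this schedule has a post-baseline observation to carry.

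Some stronger readings are tempting and are not supported:
- **Both co-primary outcomes are biased in a known direction.** Zero change is least plausible for the 6-Minute Walk Test. For the Vancouver Scar Scale the documents give no course from day 1–2 to day 10, so the direction is unknown.
- **Well-recovered patients go home early, miss the visit and receive their worst score.** The Introduction says only "Phase I cardiac rehabilitation refers to the early, in-hospital phase of recovery typically spanning the first 2–10 days for after CABG surgery", a general statement, while the trial plans a 10-day in-hospital programme. Who would miss the visit, and why, is conjecture.
- **The rule always inflates the variance.** On change scores with SD 1 and 20% missing, a mean change of 1 SD gives √(0.8 + 0.16 × 1²) = 0.98, a slight fall.
- **The Fig. 1 caption flatly contradicts Statistical methods.** It can be read as announcing both a per-protocol and an intention-to-treat analysis. It is loose wording that needs reconciling.

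**Conclusion.** The concern holds. That the rule imputes exactly zero change for every patient with a baseline but no final value follows from the two sections alone and needs no assumption.

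The size does need assumptions: missingness unrelated to outcome, 42 per arm, unit SDs and an unknown common recovery. At the planned 20% in each arm the estimate of a true effect loses one fifth, and power on final values falls by roughly 9 to 32 percentage points against observed cases across the range shown. A 10-point imbalance in missingness adds 0.1 SD of bias per SD of recovery, towards either arm. With equal missingness and no true effect, the between-group test is sound.

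The observed-case figures are a benchmark under benign missingness, not a recommended analysis. Because a stated rule determines both co-primary estimates and does not suit the stated schedule, it should be changed before the data are analysed.

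**What to change.** 1. In Statistical methods, delete last observation carried forward.
2. Make the primary analysis baseline-adjusted ANCOVA on the final value, with all randomised participants in their allocated arm. Handle missing finals by multiple imputation within arm, using baseline value, age and sex, or by an equivalent likelihood-based model.
3. Add a delta-adjusted sensitivity analysis in which imputed values are shifted by a range of amounts.
4. Reword the Fig. 1 caption so that the primary set is all randomised participants and the per-protocol set is a sensitivity analysis.

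Do not deal with missing finals by moving the final assessment to discharge or adjusting for discharge day. That would change the assessment schedule and condition on a post-randomisation variable that treatment may affect.

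The cost is rewording in two places and a little more analysis work, with no new patients or visits. ANCOVA is already named in the plan. Trial status expects recruitment to finish in August 2026, so the change can be recorded as an amendment before the final analysis.

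### Two co-primary outcomes are each tested at an unadjusted 0.05 with no statement of whether one or both must succeed, so neither the type I error nor the power of the primary claim is fixed

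*Protocol article*

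**What the plan says.** The Outcome measures section is explicit about the primary outcomes: "This trial has two co-primary outcomes: (1) scar healing measured by the Vancouver Scar Scale and (2) functional capacity measured by the 6-Minute Walk Test". Manual Muscle Testing and the PHQ-9 (the quality-of-life measure) are listed there as secondary.

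The Statistical methods section sets one threshold for everything: "A p-value of <0.05 will be considered statistically significant for all analyses". In that section, the analyses comprise within-group tests, between-group tests, ANCOVA and possible subgroup analyses. No alpha split, hierarchy or joint success criterion appears there or elsewhere in the article.

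The Sample size calculation sizes a single comparison, "assuming an effect size (d) = 0.49, α = 0.05, and power (1–β) = 0.80". It describes the effect as a "moderate clinical difference expected in primary outcomes such as functional capacity, scar healing, and quality of life", which puts quality of life among the primary outcomes.

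**The concern.** With two primary outcomes, a per-test level of 0.05 does not by itself define the error rate of the trial's primary claim. That rate depends on the success rule. An either-outcome rule inflates the type I error; a both-outcomes rule protects it and lowers the power. The protocol fixes the per-test level but not the rule.

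The primary conclusion therefore rests on an error rate above the nominal one or on a power below the stated one, and a reader cannot tell which. If the rule stays open until the data are seen, a result on one outcome only could be presented as success under one reading or as failure under the other.

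The conflict over quality of life compounds this, because even the number of primary outcomes differs between sections.

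**Working it through.** **Inputs from the protocol.** Two co-primary outcomes (Outcome measures); 0.05 for every test (Statistical methods); alpha 0.05, power 0.80, d = 0.49, 35 per group before dropout and 42 after (Sample size calculation). The tests are taken as two-sided: the sample size formula uses Zα/2, and the Statistical methods section does not state sidedness.

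**Assumption not in the protocol.** The correlation ρ between the two test statistics, shown over 0 to 0.9.

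**The plan's own figure.** For two independent means, n = 2(1.960 + 0.842)² / 0.49² = 65.4, so 66 per group (67 by the exact t-test), not 35. The figure of 35 is reproduced by a paired t-test with the listed correlation of 0.5: 0.93 / √(1.75² + 2.00² − 2 × 0.5 × 1.75 × 2.00) = 0.93 / √3.5625 = 0.493, which needs 35 pairs. That is a separate problem. What matters here is that the calculation covers one comparison at an unadjusted 0.05.

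**Reading 1: either outcome suffices.** With both null hypotheses true, familywise error = 1 − P(|Z₁| < 1.96 and |Z₂| < 1.96). For independent tests this is 1 − 0.95² = 0.0975. For correlated tests, from the bivariate normal:

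| ρ | 0 | 0.3 | 0.5 | 0.7 | 0.9 |
|---|---|---|---|---|---|
| Error | 9.75% | 9.5% | 9.1% | 8.4% | 7.0% |

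Counting only false claims in favour of ergometry, the error is 1 − 0.975² = 4.9% at ρ = 0 and 4.5% at ρ = 0.5, against a nominal 2.5%. The inflation is again close to twofold.

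If quality of life were a third primary outcome, as the Sample size calculation implies, the independent-test figure would be 1 − 0.95³ = 14.3%.

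**Reading 2: both outcomes required.** The error is at most 5%, and 0.05² = 0.25% if both nulls are true and the tests are independent. No adjustment of alpha is needed. If each outcome truly had 80% power, the joint power is 0.80² = 64% at ρ = 0 and 69% at ρ = 0.5 (bivariate normal, 0.687).

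**Cost of adjusting.** Under Holm the smaller of the two p-values must be below 0.025; if it is, the other is tested at 0.05. Single-outcome t-test power at d = 0.49:

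| Per arm | at 0.05 | at 0.025 |
|---|---|---|
| 42 | 60% | 49% |
| 35 | 52% | 41% |

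**The case against.** The strongest objection is that the protocol nowhere says success on one outcome is enough. In common usage co-primary can mean that both must succeed, and then 0.05 for each is correct. The hypothesis in the Abstract lists improvements in scar healing, strength, functional capacity and quality of life together, which fits a joint reading at least as well as a separate one. This stands. A reader might infer that the plan runs at nearly 10% error, but the documents do not support that as a flat statement. It needs an either-outcome rule, both nulls true, weakly correlated tests, and significant results counted in both directions.

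A reader might also count all four outcomes and quote 1 − 0.95⁴ = 18.5%. That figure does not bear on the primary claim: Manual Muscle Testing and the PHQ-9 are labelled secondary in the Outcome measures section, and the subgroup analyses are described as exploratory.

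Nor should the much lower joint power that follows from d = 0.49 at the planned size (36% at 42 per arm with independent t-tests, 0.602²) be charged to this point. Most of that shortfall comes from the sample size not matching two independent groups. The part due to joint testing is the fall from 80% to 64%–69%. The relevant enrolment is 42 per arm; 35 is the number before the dropout allowance.

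Finally, multiplicity rules are often left to an analysis plan, which is not at hand. That excuse is weak here, because the protocol is not silent: it fixes an unadjusted threshold for all analyses, and a later plan that split alpha would contradict it.

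**Conclusion.** The point holds as a missing success rule combined with a fixed unadjusted threshold. The consequence is one of two: a familywise error of up to 9.75% (7.0% even at ρ = 0.9) if either outcome suffices, or an error of at most 5% with a joint power of 64% to 69% in place of the stated 80% if both are required. The correlations are assumed, and the power range takes 80% per outcome at face value. The text does not establish which reading is meant. The inconsistent status of quality of life is a plain contradiction between two sections. The rule determines what the trial may conclude, so it should be settled before unblinding.

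**What to change.** Replace the threshold sentence in Statistical methods with, for example: *The two co-primary outcomes are tested with the Holm procedure at overall two-sided 0.05, and a claim may be made for each outcome that passes; secondary, within-group and subgroup results are supportive.* Holm is valid at any correlation between the outcomes.

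Alternatively, state that both outcomes must reach p<0.05 and restate the power for the joint test. Either option closes the gap; the choice depends on what the investigators intend to claim.

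In both cases, reconcile the Sample size calculation with Outcome measures on whether quality of life is primary.

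The change is one or two sentences and leaves the conduct of the trial untouched. The Trial status section gives recruitment from June 2025 to an expected end in August 2026, with no amendments so far; the change should be dated and made before unblinding. Holm's price is the loss of first-step power shown above. The price of the joint rule is the lower power that must then be declared.
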